**12.2.2. Visit 2 (1 week: Randomization and Administration of the Investigational Product)**

This visit will be conducted within 2 weeks after Visit 1, and if there are tests not performed at Visit 1, they will be checked over the duration of screening. Evaluations to be made at this visit are as follows:

- 1) Any change in medical history and concomitant medication will be checked in comparison to last visit.
- 2) Physical examination will be carried out.

- 
- 3) Vital signs (blood pressure, pulse rate, respiration, and body temperature), height, and body weight will be measured.
  - 4) Final assessment will be made with regard to whether the patients meeting the inclusion/exclusion criteria have been selected by putting together the results of all the tests and evaluations including clinical laboratory tests.
  - 5) Randomization will be conducted.
  - 6) SIB test will be conducted.
  - 7) CDR-SOB test will be conducted.
  - 8) CIBIC-Plus test will be conducted.
  - 9) NPI test will be conducted.
  - 10) ADCS-ADL-severe test will be conducted.
  - 11) The investigational product will be administered (Whether there is any AE will be observed for 30 minutes after the administration).
  - 12) The next visit date (Visit 3) will be set.

**12.2.3. Visits 3~5 (2, 3, and 4 weeks  $\pm$  2 days ; Administration of the Investigational Product)**

This visit will be conducted at intervals of 1 week after Visit 2, and evaluations to be made at this visit are as follows:

- 1) Any change in concomitant medication will be checked in comparison to last visit.
- 2) Physical examination will be carried out.
- 3) Vital signs (blood pressure, pulse rate, respiration, and body temperature), height, and body weight will be measured.
- 4) Incidence of AEs and the details will be investigated.
- 5) The investigational product will be administered (Whether there is any AE will be observed for 30 minutes after the administration).
- 6) The next visit dates (Visits 4, 5, and 6) will be set.

**12.2.4. Visits 6~8 (6, 8, and 10 weeks  $\pm$  3 days ; Administration of the Investigational Product)**

This visit will be conducted at intervals of 2 weeks after Visit 5, and evaluations to be made at this visit are as follows:

- 1) Any change in concomitant medication will be checked in comparison to last visit.
- 2) Physical examination will be carried out.

- 
- 3) Vital signs (blood pressure, pulse rate, respiration, and body temperature), height, and body weight will be measured.
  - 4) Incidence of AEs and the details will be investigated.
  - 5) The investigational product will be administered (Whether there is any AE will be observed for 30 minutes after the administration).
  - 6) The next visit dates (Visits 7, 8, and 9) will be set.

**12.2.5. Visit 9 (12 weeks  $\pm$  3 days ; Administration of the Investigational Product)**

This visit will be conducted at 12 weeks after Visit 1, and evaluations to be made at this visit are as follows:

- 1) Any change in concomitant medication will be checked in comparison to last visit.
- 2) Physical examination will be carried out.
- 3) Vital signs (blood pressure, pulse rate, respiration, and body temperature), height, and body weight will be measured.
- 4) Laboratory tests will be conducted.
- 5) SIB test will be conducted.
- 6) K-MMSE test will be conducted.
- 7) CDR-SOB test will be conducted.
- 8) CIBIC-Plus test will be conducted.
- 9) NPI test will be conducted.
- 10) GDS test will be conducted.
- 11) ADCS-ADL-severe test will be conducted.
- 12) Incidence of AEs and the details will be investigated.
- 13) The investigational product will be administered (Whether there is any AE will be observed for 30 minutes after the administration).
- 14) The next visit date (Visit 10) will be set.

**12.2.6. Visits 10~14 (14, 16, 18, 20, and 22 weeks  $\pm$  3 days ; Administration of the Investigational Product)**

This visit will be conducted at intervals of 2 weeks after Visit 9, and evaluations to be made at this visit are as follows:

- 1) Any change in concomitant medication will be checked in comparison to last visit.
- 2) Physical examination will be carried out.

- 
- 3) Vital signs (blood pressure, pulse rate, respiration, and body temperature), height, and body weight will be measured.
  - 4) Incidence of AEs and the details will be investigated.
  - 5) The investigational product will be administered (Whether there is any AE will be observed for 30 minutes after the administration).
  - 6) The next visit dates (Visits 11, 12, 13, 14, and 15) will be set.

**12.2.7. Visit 15 (24 weeks  $\pm$  3 days ; Administration of the Investigational Product)**

This visit will be conducted at 24 weeks after Visit 1, and evaluations to be made at this visit are as follows. Even the patients who drop out of this clinical trial should undergo the tests conducted at Visit 15.

- 1) Any change in concomitant medication will be checked in comparison to last visit.
- 2) Physical examination will be carried out.
- 3) Vital signs (blood pressure, pulse rate, respiration, and body temperature), height, and body weight will be measured.
- 4) Laboratory tests will be conducted.
- 5) SIB test will be conducted.
- 6) K-MMSE test will be conducted.
- 7) CDR-SOB test will be conducted.
- 8) CIBIC-Plus test will be conducted.
- 9) NPI test will be conducted.
- 10) GDS test will be conducted.
- 11) ADCS-ADL-severe test will be conducted.
- 12) Incidence of AEs and the details will be investigated.
- 13) The investigational product will be administered (Whether there is any AE will be observed for 30 minutes after the administration).
- 14) For female patients of childbearing age, pregnancy test will be conducted.
- 15) The next visit date (Visit 16) will be set.

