**TRIAL FLOW CHART**

|                                                                           | Screening  | Duration of Treatment |    |    |    |    |    |     |     |     |     |     |     |     |     | End of Trial |
|---------------------------------------------------------------------------|------------|-----------------------|----|----|----|----|----|-----|-----|-----|-----|-----|-----|-----|-----|--------------|
| Visit                                                                     | V1         | V2                    | V3 | V4 | V5 | V6 | V7 | V8  | V9  | V10 | V11 | V12 | V13 | V14 | V15 | V16          |
| Week                                                                      | ≤ -2 weeks | W1                    | W2 | W3 | W4 | W6 | W8 | W10 | W12 | W14 | W16 | W18 | W20 | W22 | W24 | W28          |
| Visit window                                                              |            |                       | ±2 | ±2 | ±2 | ±3 | ±3 | ±3  | ±3  | ±3  | ±3  | ±3  | ±3  | ±3  | ±3  | ±3           |
| Patient consent
consent and provision
of screening number           | O          |                       |    |    |    |    |    |     |     |     |     |     |     |     |     |              |
| Checking the
inclusion/exclusion
criteria                           | O          | O                     |    |    |    |    |    |     |     |     |     |     |     |     |     |              |
| Randomization and
provision of
registration number                  |            | O                     |    |    |    |    |    |     |     |     |     |     |     |     |     |              |
| Demographic
information                                                | O          |                       |    |    |    |    |    |     |     |     |     |     |     |     |     |              |
| Checking medical
history                                               | O          | O                     |    |    |    |    |    |     |     |     |     |     |     |     |     |              |
| Height                                                                    | O          |                       |    |    |    |    |    |     |     |     |     |     |     |     |     |              |
| Body weight                                                               | O          | O                     | O  | O  | O  | O  | O  | O   | O   | O   | O   | O   | O   | O   | O   | O            |

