### **6.1. Primary Efficacy Endpoint**

- 1) Change from baseline in the Severe Impairment Battery (SIB) score at Visit 15 (Week 24).

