### 7.2.2. Duration of Administration

The investigational product and placebo are subcutaneously administered by SC injection once weekly for Visits 2 to 5 (Weeks 1 to 4) and once every 2 weeks for Visits 6 to 15 (Weeks 6 to 24).

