#### **12.1.1.1. SIB (Severe Impairment Battery)**

SIB evaluation will be conducted at Visits 2, 9 and 15.

The SIB (Saxton et al., 1990) was developed to evaluate dementia patients with severe cognitive impairment and consists of easy and simple questions. The questionnaire consists of 50 questions for the 9 items of "orientation", "social interaction", "construction", "orienting to name", "language", "memory", "praxis", "visuo-spatial ability". The scores range from 0 to 100 points, and the better the state of the patient, the higher the score.

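### Visits 9, 15 and 16 are timed from screening while the flow chart and Visits 3 to 8 run from Visit 2, so the primary endpoint interval and one dosing interval depend on how long screening lasts

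*Protocol*

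**What the plan says.** The primary endpoint (section 6.1) is "Change from baseline in the Severe Impairment Battery (SIB) score at Visit 15 (Week 24"). Section 12.1.1.1 fixes when the scale is given: "SIB evaluation will be conducted at Visits 2, 9 and 15". There is no SIB at screening, so its baseline is Visit 2, the visit of randomization and first dose.

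The timing rules are as follows.

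- **Visit 2** (12.2.2): "This visit will be conducted within 2 weeks after Visit 1". The flow chart places Visit 1 up to 2 weeks before treatment and labels Visit 2 as W1.
- **Visits 3 to 5** (12.2.3): weekly, counted from Visit 2.
- **Visits 6 to 8** (12.2.4): "This visit will be conducted at intervals of 2 weeks after Visit 5", hence counted from Visit 2 through the chain.
- **Visit 9** (12.2.5): "This visit will be conducted at 12 weeks after Visit 1".
- **Visits 10 to 14** (12.2.6): two-weekly, counted from Visit 9.
- **Visit 15** (12.2.7): "This visit will be conducted at 24 weeks after Visit 1".
- **Visit 16** (12.2.8): 28 weeks ±3 days, again from Visit 1.

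The flow chart gives Visits 7 to 16 the labels "W8 | W10 | W12 | W14 | W16 | W18 | W20 | W22 | W24 | W28". On dosing, section 7.2.2 says "once every 2 weeks for Visits 6 to 15 (Weeks 6 to 24"), and section 11.1 describes four weekly doses followed by ten two-weekly doses, 14 in all.

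**The concern.** Two anchors are in use. Visits 3 to 8 follow the date of Visit 2. Visits 9, 15 and 16 follow the date of Visit 1, and Visits 10 to 14 inherit that anchor from Visit 9. The gap between the two anchors is the screening length, which varies from patient to patient.

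Two things are affected. The first is the interval over which the primary SIB change is measured, because its baseline sits on one anchor and its endpoint on the other. The second is the dosing interval where the anchor switches, between Visits 8 and 9, which can no longer be two weeks for every patient. These sentences tell sites when to assess and dose patients, so a site that obeys one of them can be outside the window set by another.

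**Working it through.** **Inputs.** Screening length *s* (days from Visit 1 to Visit 2) is 0 to 14, from section 12.2.2. Anchors are from sections 12.2.3 to 12.2.8, and week labels and the ±3-day window from the flow chart. All days below are counted from Visit 2, with each visit taken at its target date.

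**Step 1: the flow chart on its own.** With Visit 2 at W1, day = 7 × (W − 1).

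- Visit 8: 7 × 9 = 63
- Visit 9: 7 × 11 = 77
- Visit 15: 7 × 23 = 161
- Visit 16: 7 × 27 = 189

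Dosing visits 2 to 15 number 14. Their intervals are three of 1 week and ten of 2 weeks, and 3 + 20 = 23 weeks. This reproduces the dosing schedule in 7.2.2 and 11.1. Because Visit 2 is W1 and not W0, Week 24 in the chart is 23 weeks after the SIB baseline.

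**Step 2: the section 12.2 text.**

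- Visit 5: 3 × 7 = 21
- Visit 8: 21 + 3 × 14 = 63, as in the chart
- Visit 9: 84 − *s*
- Visit 14: (84 − *s*) + 5 × 14 = 154 − *s*
- Visit 15: 168 − *s*
- Visit 16: 196 − *s*

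The Visit 8 to Visit 9 interval is (84 − *s*) − 63 = 21 − *s*. Visit 14 to Visit 15 stays at 14 days and Visit 15 to Visit 16 at 28 days, so Visit 8 to Visit 9 is the only dosing interval disturbed.

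**Step 3: results by screening length.**

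| *s* (days) | Visit 8 to 9 (days) | Visit 9 (day) | Visit 15 (day) | Visit 15, text minus chart |
|---|---|---|---|---|
| 0 | 21 | 84 | 168 (24.0 wk) | +7 |
| 3 | 18 | 81 | 165 | +4 |
| 4 | 17 | 80 | 164 | +3 |
| 7 | 14 | 77 | 161 (23.0 wk) | 0 |
| 10 | 11 | 74 | 158 | −3 |
| 11 | 10 | 73 | 157 | −4 |
| 14 | 7 | 70 | 154 (22.0 wk) | −7 |

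The difference from the chart is 7 − *s* for Visits 9, 15 and 16. It is zero only at *s* = 7 and exceeds 3 days when *s* is below 4 or above 10.

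**Step 4: adding the window.** Under the text, the SIB interval is bounded by 154 − 3 = 151 and 168 + 3 = 171 days. Under the chart it is 161 ±3, that is 158 to 164.

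**Step 5: scales with a Visit 1 baseline.** The flow chart footnote takes K-MMSE and GDS baseline from Visit 1. With that result used, the text gives them a fixed 168 days to Visit 15, while the chart gives 161 + *s*, or 161 to 175 days. Neither anchor fixes the interval for every scale.

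**The case against.** **The rest of the protocol describes one regular schedule.** The flow chart, the week labels in the section 12.2 headings, 7.2.2, 11.1 and the synopsis all fit together, so the 22 to 24 weeks applies only where the three anchor sentences are followed literally. That condition stands. But the same anchor appears in three separate sections, each an operative instruction, and nothing says that the chart prevails. One might read the week labels as weeks since Visit 1, which would remove the conflict. That needs a fixed one-week screening, whereas the flow chart and 12.2.2 allow anything up to two weeks.

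**The extremes are unlikely.** The span from 151 to 171 days joins same-day screening to a full 14 days, each with a full window error. Eligibility and laboratory results must be in hand before treatment, so *s* = 0 would be unusual. This stands: the span is an outer bound, not an expected spread.

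**The effect on the result is probably small.** The protocol gives neither a rate of SIB decline nor a standard deviation. As an illustration only, assume a decline of 5 to 10 points over 24 weeks and screening uniform over 0 to 14 days. The SD of screening length is 14/√12 = 4.04 days, or 0.58 week. The added SD is then 0.58 × 5/24 = 0.12 to 0.58 × 10/24 = 0.24 points on a 0 to 100 scale. This point largely stands, and no loss of power is claimed.

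**Stronger readings that the document does not support.** A reader might infer that timing deviations will remove patients from the per-protocol set. Section 15.1.7 does not list visit timing among its serious violations and keeps minor ones in that set after blind review. Section 15.1.1 defines the set more broadly, so exclusion is not impossible, but it does not follow. The main efficacy analysis uses the full analysis set in any case. A reader might also infer a bias between arms, but screening ends before treatment starts, so its length should not differ systematically by arm. Finally, one might ask for analysis windows or an analysis by actual SIB date. Windows belong to the SAP, which is not at hand, and the planned t-test or Wilcoxon test of change at Visit 15 does not use dates.

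**Conclusion.** The contradiction is real and concerns both the primary endpoint visit and dosing dates. Taken literally, the section 12.2 text places the primary SIB assessment 168 − *s* days after its baseline, nominally 22 to 24 weeks, against 23 weeks under the flow chart. It makes the Visit 8 to Visit 9 dosing interval 21 − *s* days, nominally 1 to 3 weeks, against the stated two. The two sets of targets are further apart than the ±3-day window whenever screening lasts under 4 or over 10 days.

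These figures assume that *s* can take any value from 0 to 14 and that each visit falls on its target date. How often screening departs from one week is not stated. The consequence is an inconsistently timed endpoint, some added variability of unknown but probably small size, and instructions that sites cannot all satisfy at once. The error does not invalidate the trial, but it should be corrected.

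**What to change.** Reconcile sections 12.2.5, 12.2.7 and 12.2.8 with the flow chart, 7.2.2 and 11.1. One stated anchor should govern all visits after randomization and their windows, and the interval from baseline SIB to Visit 15 should be the same for every patient. Which administration schedule is intended is for the sponsor to confirm.

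The amendment should also acknowledge that K-MMSE and GDS take their baseline at Visit 1, so their interval will still vary with screening length if Visit 2 becomes the anchor.

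The cost is a clarifying amendment and a letter to sites, with no added visits.

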| Fatigue                               | 8                           |
| Etc.                                  | 49                          |
| Infections and infestations           | 196/1,418 cases
(13.71%) |
| Biliary sepsis                        | 39                          |
| Sepsis                                | 22                          |
| Infection                             | 20                          |
| Lower respiratory tract infection     | 17                          |
| Pneumonia                             | 15                          |
| Cellulitis                            | 10                          |
| Urinary tract infection               | 7                           |
| Liver abscess                         | 5                           |
| Etc.                                  | 61                          |

In addition to SAEs reported frequently, erythema, soreness, pain, etc. at the injection site were reported. The injection site reactions are the side effects occurring frequently when GV1001 is administered. Generally, the reactions occur within 24 hours after the administration of GV1001 and disappear within days. Therefore, the above adverse events may occur even in this clinical trial.

If immunity-related adverse events specific to this drug appear, the administration of this drug should be discontinued, and treatments of symptoms or supportive treatments should be carried out according to the investigator's judgment while the immune response is decreasing.

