#### 14. CRITERIA OF TRIAL DISCONTINUATION AND DROPOUTS

##### 14.1. Criteria of Trial Discontinuation and Dropouts

Patients are free to withdraw from this clinical trial at their request at any time. The investigator or sponsor is also free to withdraw a patient at any time for the reasons of safety, action, and administration.

The investigator should inquire of the patient about a cause of dropout in this trial and ask him/her to make the last visit so that all tests can be performed as scheduled at Visit 15. If the patient does not make the scheduled visit, the investigator should make every effort to contact him/her and document results of tests related to the patient as best he/she can. The investigator should also do his/her best to identify the reason why the patient dropped out of this trial, ask for the return of unused investigational products, and continue to monitor the patient (follow-up) with regard to unresolved adverse events.

In case the patient withdraws his/her consent, further evaluation and additional data collection will no longer be possible, even if agreement to the personal information disclosure is withdrawn. All data collected prior to the withdrawal of consent can be continuously kept and used by the sponsor.

The following are the cases where the patient can stop and drop out of this clinical trial over the duration of clinical trial.

- ① In case the patient or the patient's legally authorized representative agrees to withdraw the consent to participation in this clinical trial
- ② In case the patient is found to have violated the inclusion/exclusion criteria
- ③ In case the patient is found to have violated the important study plan specified in the clinical trial protocol
- ④ In case the continuous administration and observations are not appropriate for this trial due to AE or SAE according to the investigator's judgment
- ⑤ In case the investigator has difficulty in administering the investigational product to the patient
- ⑥ In case the investigator judges that follow-up of the patient is impossible
- ⑦ In case the patient took the prohibited concomitant medication; or in case the investigator judges that the patient needs treatment with the prohibited concomitant medication
- ⑧ In case the investigator decides that it is not appropriate for the patient to continue to participate in this trial

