## 16.2. Collection and Recording of Adverse Events

- After randomization, AEs should be collected over the duration of this clinical trial from the time points since the administration of the investigational product to the final visit.
- AEs should be reported including the names of AEs, duration (start date and date of disappearance), severity, causal relationship with the investigational product, related measures, results, remedial treatment, and whether to have SAEs.
- When recording AEs, the investigator should record a comprehensive diagnostic name or symptom using standard medical terms rather than recording each symptom or sign.
- When it comes to AEs occurring during this clinical trial, a follow-up should be carried out until they disappear, show a stable outcome, or are lost to follow up.

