**AEs occurring after the termination of treatment**

An AE considered to be due to the investigational product used in this clinical trial, even if it occurs after the termination of treatment, should be reported in accordance with the procedures above.

Contact a person in charge of safety information at GemVax & KAEL Co., Ltd. ([contact], [contact], E-mail: [[contact]](mailto:[contact]))

(1) Obligation of principal investigator

The principal investigator should immediately report to the IRB or the sponsor upon a serious ADR incurred during the clinical trial.

(2) Obligation of subinvestigator

The subinvestigator should immediately report to the principal investigator or the sponsor upon a serious ADR, etc. incurred during the clinical trial.

(3) Obligation of IRB

In case unexpected serious risks such as serious ADRs, etc. occur in patients, the IRB can determine the early termination or the temporary discontinuation of this clinical trial. In this case, the IRB should notify the director of study center or the principal investigator of the decision and the cause.

(4) Obligation of sponsor

In case a serious and unexpected ADR is reported by the principal investigator or the subinvestigator, the sponsor should submit the ADR report with an attached copy of the report submitted by the principal investigator or the subinvestigator to the Minister of Food and Drug

---

Safety within the prescribed deadline. If multiple study centers conduct this clinical trial, the sponsor should also immediately notify the relevant study centers.

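### For patients who stop early, scheduled collection of new adverse events ends at an exit visit not tied to the last dose, with no equivalent of Visit 16

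*Protocol*

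**What the plan says.** Section 7.2.2 of the Protocol puts the last planned dose at Visit 15 (Week 24). Section 12.2.8 then sets Visit 16 at Week 28, with adverse event questions, vital signs and a physical examination.

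For patients who stop early, section 12.2.7 says "Even the patients who drop out of this clinical trial should undergo the tests conducted at Visit 15". Section 14.1 tells the investigator to "ask him/her to make the last visit so that all tests can be performed as scheduled at Visit 15". Neither section says how long after the last dose this happens. Section 12.2.8 sets no version of Visit 16 for these patients.

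Section 16.2 collects adverse events "from the time points since the administration of the investigational product to the final visit". Some safety work continues beyond that:
- For events already present, section 16.2 says "a follow-up should be carried out until they disappear, show a stable outcome, or are lost to follow up", and section 14.1 asks the investigator to "continue to monitor the patient (follow-up) with regard to unresolved adverse events".
- For new events, the paragraph on events after treatment (section 16.4) keeps the reporting duty in force once treatment has ended, but only for those attributed to the product.
- Section 12.2.9 allows additional visits on request or at the investigator's discretion.

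The Visit 15 list in section 12.2.7 also contains a dose (item 13) and the setting of the Visit 16 date (item 15).

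**The concern.** Early leavers stay in the safety analysis set if they were dosed and had at least one safety evaluation (section 15.1.1). Missing safety values are not replaced (section 15.1.6). Adverse event incidence is compared between groups by chi-square or Fisher test (section 15.1.5.1), with no allowance stated for unequal follow-up. An event that nobody collects is therefore counted as no event.

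The shorter window falls only on patients who leave, and some leave for safety reasons. An adverse event or serious adverse event is one of the eight listed reasons in section 14.1, and section 7.5 ends participation for a patient whose code is broken. Section 14.2 advises patients about unexpected delayed adverse events but addresses only those who completed. If withdrawals differ by arm, the observation behind the safety comparison differs by arm too. Safety is part of the primary objective (section 6), with 30 patients per group.

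**Working it through.** **1. The plan's own figure.** Section 9.3 has 24 evaluable patients per group and 20% dropout: 24 / (1 − 0.20) = 30 per group, and 3 × 30 = 90. This reproduces the stated sample size. Planned dropouts are 90 − 72 = 18, or 6 per group.

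**2. Post-dose window for completers.** Sections 12.2.7 and 12.2.8 both count from Visit 1, so the interval is Week 28 − Week 24 = 4 weeks = 28 days. Each visit has a window of ±3 days, so the range is 28 − 6 = 22 to 28 + 6 = 34 days.

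**3. Post-dose window for early leavers.** The Protocol guarantees none. Let g be the days from last dose to exit visit. This is an assumption: I take g = 0, 7 and 14, because 7 and 14 days are the two dosing intervals. The shortfall per patient is 28 − g, and the total is 18 × (28 − g):

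| g (days) | Shortfall per patient (days) | Total over 18 (patient-days) |
|---|---|---|
| 0 | 28 | 504 |
| 7 | 21 | 378 |
| 14 | 14 | 252 |
| 28 | 0 | 0 |

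These totals are upper bounds for each g. They assume that all 18 were dosed and that none withdrew consent; section 14.1 rules out further collection after consent withdrawal.

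**4. Scale.** Completers are observed from Week 1 to Week 28: 27 × 7 = 189 days, and 72 × 189 = 13,608 patient-days. The shortfall relative to that is 252 / 13,608 = 1.9% to 504 / 13,608 = 3.7%.

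**5. Which events are exposed.** The Synopsis compares the proportions of patients with adverse events, and with serious adverse events, once or more.
- A patient withdrawn for an adverse event already counts in the first comparison; a later event does not change it.
- The same patient's first serious event after exit would change the serious-event comparison.
- Additional event terms would change the tabulation by organ system and term in section 15.1.5.1.
- For a patient who left for another reason, a first event after exit would change the overall comparison.

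**6. The Visit 15 list, read both ways.**
- Only the tests apply to early leavers: items 13 and 15 drop out. There is no dose and no Visit 16, and the gap stands.
- The whole list applies: item 15 sets Visit 16 and closes the gap, but contradicts the last-visit wording in section 14.1. Item 13 then conflicts with section 13, where for immunity-related events "the administration of this drug should be discontinued", and with section 16.5 on pregnancy.

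The wording in sections 12.2.7 and 14.1 favours the first reading, but the exception is only implicit.

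**The case against.** The strongest reply is that safety follow-up does not stop at exit, and that is correct. Unresolved events are followed, and a product-attributed event is to be reported "even if it occurs after the termination of treatment, should be reported in accordance with the procedures above". Section 16.3.2 treats five of its six causality categories as related, so if that scale governs, few new events would be filtered out by causality alone. Section 16.4 also requires serious events to be reported regardless of causality over the duration of the trial, though whether that reaches a patient who has left is open. These provisions narrow the gap. They do not close it, because each depends on the site learning of the event, and no contact is scheduled.

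The timing is also uncertain. Section 14.1 could be read as asking the patient back at Week 24. Anyone last dosed at or before Week 20 would then have at least 28 nominal days. That reading shrinks the gap, but it still does not tie collection to the last dose.

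Three stronger readings are tempting and not supported. A reader might infer that the plan gives early leavers a dose because the Visit 15 list contains one; both sections that address these patients direct them only to tests. A reader might infer that section 13 warns of a delayed immune reaction; it speaks of immunity-related events and gives no delay, and the delayed-event wording is in section 14.2. A reader might infer that the gap makes GV1001 look safer; that would require withdrawals to differ by arm, which the documents cannot show.

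**Conclusion.** The point holds in a limited form. Completers have scheduled collection of new adverse events for about 28 days after the last dose (22 to 34 with visit windows). On the more natural reading of sections 12.2.7, 14.1 and 16.2, early leavers have no guaranteed interval.

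The size is small: 14 to 28 days per leaver if exit falls 0 to 14 days after the last dose, hence at most 252 to 504 patient-days over 18 planned dropouts, and less after consent withdrawals. This rests on the planned 20% dropout and on assumed exit timing. The direction of any bias is unknown in advance. It is still worth correcting, because the shortfall falls wholly on early leavers, the groups are small, and the correction is cheap. The Visit 15 list is a separate matter of wording to be reconciled.

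**What to change.** In sections 12.2.8, 14.1 and 16.2, apply the Protocol's own Visit 16 post-dose interval to adverse event collection, regardless of causality, for every dosed patient who stops early and has not withdrawn consent. A visit or a call to the guardian would serve. State in section 14.1 when the exit visit takes place, so that it cannot be read both as an immediate visit and as a return at Week 24.

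Separately, reconcile items 13 and 15 of the Visit 15 list with sections 13, 14.1 and 16.5, so that it is explicit which items apply to early leavers. This asks for consistent wording only; what the dosing rule should be is for the sponsor and investigators.

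The cost is an amendment to the wording and one extra contact for up to about 18 patients.
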